## Abstract

**Background:**

Early lifestyle intervention with overweight and obese adolescents could help to avoid serious health events in early adulthood, ultimately alleviating some of the strain on the public health system due to obesity-related morbidity. Commercial weight loss programs have wide reach into the community setting, and have demonstrated success in long term weight management in adults, beyond that of current public health care. Commercial weight-management programs have not been evaluated as a method of delivery for overweight and obese adolescents. This study aims to evaluate the efficacy of a new adolescent weight management program in a commercial environment.

**Methods:**

One hundred and forty adolescents, 13 to 17 years old, will be randomised to either a weight management program intervention or a wait-listed group for 12 weeks. The commercial program will consist of a combined dietary and lifestyle approach targeting improved health behaviours for weight-loss or weight-stability. Participants will be overweight or obese (above the 85^th^ percentile for BMI) and without existing co-morbidities. Outcome measures will be assessed at baseline and after 12 weeks. Primary outcome measures will be changes in BMI Z-score and waist-height ratio. Secondary outcome measures will include changes in behaviour, physical activity and psychosocial wellbeing. Intervention participants will be followed up at 6 months following completion of the initial program. Ethics approval has been granted from the Monash University Human Research Ethics Committee (CF11/3687–2011001940).

**Discussion:**

This independent evaluation of a weight management program for adolescents, delivered in a commercial setting, will provide initial evidence for the effectiveness of such programs; which may offer adolescents an avenue of weight-management with ongoing support prior to the development of obesity related co-morbidities.

**Trial registration:**

The protocol for this study is registered with the International Clinical Trials Registry ISRCTN13602313.

## Background

Australian prevalence of overweight and obesity in childhood and adolescence increased from 20.9 % in 1995 to 24.7 % in 2008 [1]. While the trend has started to stabilise, a significant proportion (25.7 % in 2012) of Australian children and adolescents aged 5 to 17 years, remain overweight or obese [1]. Within sub-populations the prevalence can be even higher, for example 31 % of children living in lower socioeconomic status (SES) areas, including rural areas are overweight or obese compared to 18 % of those living in the highest SES areas [2].

Overweight and obese adolescents are more likely to become overweight and obese adults than healthy weight adolescents [3]. Additionally, obesity-related cardiovascular disease (CVD) risk markers present in adolescence are predictive of adult, obesity related morbidity [4]. A study in Denmark observed that every 1 unit increase in body mass index (BMI) Z-score from age 7 to 13 years in boys and 10 to 13 years in girls, significantly increases the risk of a cardiovascular event in adulthood [5]. A 2001 Australian report suggested that interventions that result in as little as 5 kg weight loss in all overweight and obese individuals could lower the total prevalence of overweight and obesity by 15 % [6]. Thus, adolescent weight management is a significant, modifiable risk factor for the development of cardiovascular morbidity that could lead to premature mortality in adult life [7–9].

There have been two Cochrane reviews of childhood obesity management. The 2009 Cochrane Review considered interventions for treating obesity in children. It included a total of six weight-loss dietary intervention studies (*n* = 350 participants across age ranges) demonstrating overall beneficial effects of weight-loss on adiposity and BMI Z-score [10]. Twelve physical activity intervention studies were also included, which generally reported no significant change in BMI Z-score or adiposity [10]. Meta-analyses of lifestyle interventions demonstrated a favourable effect on BMI Z-score at 6 months [mean difference (MD) = -0.06 (95 % CI -0.12,–0.01)] in children aged less than 12 years, and in those over 12 years of age [MD-0.14 (95 % CI-0.17,–0.12)]. Parental involvement was noted to be an ingredient for successful intervention. However, the report highlighted the scarcity of studies in the adolescent age range.

The more recent 2011 Cochrane Review focused on interventions for preventing obesity in children and used BMI Z-score as a key outcome measure. The Review demonstrated the very different effects of weight management programs in children compared to adults, with data being abstracted and grouped by age rather than by intervention type. Most new studies included in 2011 were obesity prevention studies in children, the majority of which took place in schools. In the adolescent age group (13 to 18 years), analysis of ten studies demonstrated an overall BMI change of -0.09 kg/m^2^ (95 % CI-0.20, 0.03) [11]. However a high level of heterogeneity between studies was observed potentially due to inconsistent levels adiposity across studies as different cut-offs and anthropometric measures were applied. Further, the authors stressed an increasing awareness of the need for weight loss maintenance, and recommended that future studies monitor the effectiveness of programs in the longer-term [11].

A retrospective study that examined the long term effects of a weight management program for individuals (aged 1 to 18 years), delivered by physicians and dietitians in a primary care setting, demonstrated significant reductions in BMI Z-score [MD-0.16 (95 % CI not reported)], and participants subsequently showed improvements in several CVD risk factors such as LDL-cholesterol (*p* = 0.02), 2 h plasma glucose (*p* = 0.004) and peak insulin levels (*p* = 0.04) after a 2 year period [12]. Those who attended sessions more frequently exhibited better results. Improved blood pressure has also been observed in children and adolescents (aged 7 to 15 years) 2 years following an intensive 3-month dietary intervention with a strong follow-up program, that reduced BMI Z-score by-0.16 (95 % CI-0.22,–0.09) at 3 months [13].

Whilst programs delivered within primary care settings are modestly successful, publicly funded health systems in Australia tend to only accommodate individuals with existing obesity-related comorbidities. There are few treatment options for overweight and obese adolescents without complications. Early behavioural intervention targeted at reducing weight with longer-term maintenance could help reduce the numbers of young patients presenting to the public health system with serious weight-related health events. Evidence suggests obese young people who successfully lose weight do not have obvious complications arising from their obesity, such as insulin resistance [14].

Randomised controlled trials have demonstrated the superiority of commercially delivered programs for weight management in adults, when compared with usual care through the health service system [15–17]. Commercial weight loss programs are successful in initiating and maintaining long term weight loss in adults [18] and may also be a successful setting for weight management adolescents. Collaboration between commercial organisations and primary care facilities may be an efficacious strategy to deliver weight management programs on a large scale [19]. Commercial weight management programs can offer ongoing, long term support that cannot be provided by health professionals in primary care and has a wide reach including rural areas and they have the ability to be accessible to individuals within the population that are unable to access primary medical services for weight management [20]. Despite evidence for the benefits from an intensive multifactorial approach to weight-management in adolescents [10, 11, 21], no study to date has examined commercially available and delivered weight management programs specifically tailored to the needs of adolescents.

Jenny Craig Weightloss Centres Pty Ltd, has developed a new 12-week adolescent weight management program, ‘JenMe’. The program involves weekly face to face sessions with a Jenny Craig-trained consultant that includes dietary and behavioural education as well as monitoring of the progress of the adolescents. Menus and foods are provided initially, with support for the adolescent to eventually develop skills in their own menu planning. On completion of the 12 week program on-going support is available that can be tailored to the individual’s needs. The program has not yet been evaluated for efficacy, an essential first step in supporting the claim of an evidence-based approach to weight management in young people. This study aims to address this gap.

We propose to evaluate a commercially delivered adolescent weight management program ‘JenMe’; for efficacy. We know that lifestyle interventions for children are effective in the short term but there are few studies that examine the long term prognosis of short term weight loss and the ability of adolescents to maintain that weight loss over time. Data from the 6-month diet and lifestyle ‘Eat Smart’ intervention for Australian adolescents compared favourably with previously published data (BMI Z-score MD-0.12 (SD 0.10) at 3 months) [10], but early follow up data have already began to show a plateau in weight loss followed by some weight re-gain. Hence, the current study proposes to follow intervention participant weight management for 6 months after completion of the 12 week program.

This study will be the first to assess an adolescent weight management program that is conducted in a commercial environment. Its findings will inform the literature in the field of adolescent weight-loss and management, and has the potential to unveil an effective solution to adolescents seeking weight management in a community setting.

## Methods

### Study design and participants

The current study is a multicentre, parallel-group randomised controlled trial. Adolescent boys and girls aged 13 to 17 years who apply to join the commercial weight management program will be screened for eligibility to participate. Individuals who do not meet the health screen requirement, a standard practice for enrolment to Jenny Craig weight management programs, will not be eligible for inclusion in the study. Exclusion criteria of the program include being aged less than 13 years or greater than 17 years; having diagnosed diabetes; being pregnant; having given birth to a child during adolescence; having a medical condition or using medications related to weight co-morbidities (except asthma). Individuals who have a BMI Z-score of ≥ 1.282, indicating that they are above the 85^th^ percentile for BMI for their age and gender, will be invited to participate in the study. Participants will be randomised into either the treatment group or the wait-listed control group. The treatment group will enter the weight management program immediately, and the control group will be wait-listed for 12 weeks. Figure 1 shows the study flow. Behavioural questionnaires and diaries will be completed during the week prior to the first consultation where anthropometric characteristics of participants will be recorded. The same questionnaires and diaries will be repeated during week 12 (the final week of the program for participants in the interventions group), and participants will again have anthropometric characteristics recorded at the end of week 12. Primary outcome measures will include changes in BMI Z-score and waist to height ratio. Secondary outcome measures will include changes in physical activity levels, behaviour and psychosocial wellbeing. Participants will have the option to volunteer to have further cardio-metabolic risk factors and body composition examined. All experimental procedures are being conducted in accordance with the Declaration of Helsinki and were formally approved by the Monash University Human Research Ethics Committee (CF11/3687–2011001940).

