**Fig. 1 Fig1:**
[figure not shown]
Study flow design. One hundred and forty adolescents (13 to 17 years, BMI Z-score ≥ 1.282) will be recruited and randomised 1:1 to either the intervention or wait-listed control group. The intervention group will receive a 12 week commercial weight management program. The wait-listed control group will be offered the program after the control period (12 weeks)

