### Sample size calculations

For the purpose of sample size estimation, the primary outcome of this study was difference in BMI Z-score at 12 weeks. Our own pilot data, and data from the largest RCT in obese adolescents yet published (209 children aged 8-16 with BMI > 95^th^ percentile; Savoye 2007) suggest the standard deviation in BMI Z-score in a non-passive weight loss intervention will be approximately 0.27. Assuming a 2-sided 0.05 significance level, a sample size of 52 participants per group would provide 80 % power to detect a clinically important treatment difference of 0.15 BMI Z-score. To account for a 25 % drop-out, we plan to enrol 70 participants in each group.

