### Outcomes

#### Anthropometry

All participants will have their baseline weight, height, waist, and body composition (using bioelectric impedance analysis (BIA); BODYSTAT Quad Scan 4000, BODYSTAT Ltd., Douglas, Isle of Man, UK) measured by trained Jenny Craig consulting staff using standard operating procedures. BMI Z-score will be calculated by the lambda-mu-sigma (LMS) method using Centre for Disease Control reference data (http://www.cdc.gov/growthcharts/percentile_data_files.htm) which takes into account age and gender. Participants will be required to self-assess their pubertal status using the Tanner stages of puberty scale [23, 24]. The intervention group will have weekly weight measurements, height measured every 4 weeks and waist and body composition assessed by BIA measured at 0 and 12 weeks. Wait-listed control participants will have all measurements taken at 0 and 12 weeks only.

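### The entry cut-off of BMI Z-score ≥ 1.282 marks the 90th percentile, not the 85th percentile the protocol gives for it

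*Protocol article*

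**What the plan says.** The body-size entry rule appears in three places in the protocol article.

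- **Study design and participants** invites individuals with a "BMI Z-score of ≥ 1.282, indicating that they are above the 85^th^ percentile for BMI", for age and gender. Number and percentile stand together here, the percentile being given as what the number means.
- **Fig. 1 legend** gives only the number: "One hundred and forty adolescents (13 to 17 years, BMI Z-score ≥ 1.282) will be recruited and randomised 1:1".
- **Abstract, Methods** gives only the percentile: "Participants will be overweight or obese (above the 85^th^ percentile for BMI) and without existing co-morbidities".

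The Anthropometry section fixes how the score is obtained: "BMI Z-score will be calculated by the lambda-mu-sigma (LMS) method using Centre for Disease Control reference data". No section says that a threshold stricter than the 85th percentile was chosen, or why.

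**The concern.** The value 1.282 is familiar as the standard normal deviate for 90 %, not 85 %. If that is what it means here, the article holds two entry rules that are not equivalent. Someone who reads only the abstract and someone who reads only Fig. 1 would screen different adolescents.

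This is the trial's only entry criterion on body size. If the number is applied, the mildest overweight band is missing from the trial while the abstract describes a population that includes it, and the results would be presented as covering adolescents who could not enter. If some centres worked from the percentile and others from the Z-score, eligibility would differ by centre. The article does not show that this happened. However, screening is done by consultants in centres across several states and territories (Recruitment and randomisation), so the rule needs to be unambiguous.

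**Working it through.** **Inputs**

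- Cut-off: Z ≥ 1.282 (Study design and participants; Fig. 1 legend).
- Stated meaning: above the 85th percentile (Study design and participants; Abstract).
- Construction of Z: LMS method on CDC reference data (Anthropometry).

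**Step 1. Conversion.** The LMS method transforms BMI so that Z is standard normal within each age and gender group of the reference population. Hence percentile = 100 × Φ(Z), where Φ is the standard normal distribution function.

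**Step 2. Try to reproduce the stated figure.**

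| Reading | Result |
|---|---|
| Percentile at the stated cut-off, Φ(1.282) | 0.9001, the 90.0th percentile |
| Z at the stated percentile, Φ⁻¹(0.85) | 1.0364 |
| Z at the 90th percentile, Φ⁻¹(0.90) | 1.2816 |
| Central area, 2Φ(1.282) − 1 | 0.8002 |
| Two-sided 85 % limit, Φ⁻¹(0.925) | 1.4395 |

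None of these readings links 1.282 with 85 %. Rounding does not explain it either, since 1.2816 rounds to 1.282 and is the 90th percentile to three decimals.

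**Step 3. Size of the gap.** On the Z scale the two cut-offs differ by 1.282 − 1.036 = 0.246. In the reference population:

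- share above the 85th percentile: 1 − 0.85 = 0.150
- share between the 85th percentile and Z = 1.282: 0.9001 − 0.8500 = 0.0501
- excluded fraction of those above the 85th percentile: 0.0501 / 0.150 = 0.334

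**Step 4. Does it carry over to the sample size?** The inputs in Sample size calculations are an SD of 0.27, a difference of 0.15, two-sided 5 % and 80 % power.

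- Normal approximation: n = 2 × (1.960 + 0.842)² × 0.27² / 0.15² = 50.9, so 51 per group.
- The noncentral t distribution gives power of 0.793 at 51 and 0.801 at 52 per group, which reproduces the planned 52.
- Drop-out: 52 / 0.75 = 69.3, so 70 per group, as planned.

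The cut-off enters none of these formulas, so the planned numbers stand.

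**The case against.** The strongest reply is that the text is not false. Anyone with Z ≥ 1.282 is indeed above the 85th percentile, so both the sentence in Study design and participants and the abstract are true of every person enrolled. On this reading the number is the operative rule, it is the same in both places where it appears, and the percentile is only a gloss. Nowhere does the article promise that everybody above the 85th percentile will be invited.

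The one-way implication is correct, but it does not settle the matter. The percentile is offered as the meaning of the cut-off, and the abstract uses it without qualification to define the population. A reader will take the two as the same boundary, and they are not.

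Other parts of the reply do stand:

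- The one-third figure belongs to the reference population. Candidates here are adolescents seeking a weight-loss programme, and the article gives no BMI distribution for them. The share actually turned away is unknown and could be well below one third.
- An effect on recruitment speed cannot be shown from the article.
- Different screening rules between centres are a possibility, not an observed fact.
- Allocation, the baseline-adjusted analysis and type I error do not depend on the cut-off. The damage is to the definition of the population and to generalisability.

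**Conclusion.** The point holds. The cut-off of 1.282 is the 90th percentile and is mislabelled as the 85th, which is 1.036. As written, the rule silently omits the band from the 85th to the 90th percentile. In the reference population this band is 5.0 % of all adolescents and 33 % of those above the 85th percentile.

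The existence of the gap rests only on the normal conversion that LMS scores carry by construction. The 33 % rests further on applying the reference distribution, which may not describe the applicants. The article does not reveal which threshold was intended. Because this is the threshold on which entry to the trial depends, it must be corrected even though power and the internal comparison are untouched.

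**What to change.** Make the number and the label agree in all three places.

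- **If the 85th percentile was intended:** change the cut-off to a BMI Z-score of at least 1.036 in Study design and participants and in the Fig. 1 legend. The abstract can stay as it is.
- **If 1.282 was intended, or has already been used for enrolment:** keep the number and describe the population as at or above the 90th percentile in Study design and participants and in the abstract. Carry that description into the report of results.

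In either case, check which value the screening calculation in the centres actually uses. If both rules have been in use, report how many participants entered with Z between 1.036 and 1.282.

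The cost is a wording correction or a minor amendment, plus that check. The planned 52 and 70 per group need no recalculation, because the cut-off is not an input. One caution applies to the first option: the SD of 0.27 comes partly from a trial of children above the 95th percentile, so the team should confirm that it still considers this value reasonable for a population that starts lower.

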**Fig. 1 Fig1:**
[figure not shown]
Study flow design. One hundred and forty adolescents (13 to 17 years, BMI Z-score ≥ 1.282) will be recruited and randomised 1:1 to either the intervention or wait-listed control group. The intervention group will receive a 12 week commercial weight management program. The wait-listed control group will be offered the program after the control period (12 weeks)

### Sample size calculations

For the purpose of sample size estimation, the primary outcome of this study was difference in BMI Z-score at 12 weeks. Our own pilot data, and data from the largest RCT in obese adolescents yet published (209 children aged 8-16 with BMI > 95^th^ percentile; Savoye 2007) suggest the standard deviation in BMI Z-score in a non-passive weight loss intervention will be approximately 0.27. Assuming a 2-sided 0.05 significance level, a sample size of 52 participants per group would provide 80 % power to detect a clinically important treatment difference of 0.15 BMI Z-score. To account for a 25 % drop-out, we plan to enrol 70 participants in each group.

### Recruitment and randomisation

The study will be advertised within the weight management centres in Victoria, Western Australia, New South Wales and the Australian Capital Territory as well as on the company website. Potentially eligible clients will be assessed in the weight management centres by consultants, guided by dietitians and/or a general practitioner for study eligibility. If participants who meet eligibility criteria are interested in participating in the study, they will be shown an information DVD. All participants will provide written consent that will be obtained by consultants in the weight loss centres from both the adolescent and their parent or guardian. Consenting adolescents will then be recruited into the study via telephone by a researcher.

Allocation to treatment group (intervention or wait-listed control) will occur using computer-generated random numbers. Group allocation will occur off-site by a statistician with no day-to-day study involvement in the trial. Individuals will be allocated 1:1 to the intervention group or wait-listed. Randomisation of the study participants will be stratified by the weight-management centre from which they are enrolled. Within each centre, randomisation will occur in blocks of either 6 or 8. Block size will be randomly selected and unknown to anyone except the study statistician ([name]). Treatment allocation will be stored in an online database, accessible only by the study statistician, and will remain unknown until revealed to the study co-ordinator on the day each participant is allocated to a treatment group. Due to the nature of the intervention masking participants to group allocation is not possible.

